### Analyses

The effectiveness of case management will be established in multivariate multilevel analyses, according to the intention-to-treat principle. When possible, specific attention will be paid to identify subgroups of patients characterized by their profile of comorbidity in which the intervention is more effective than in other subgroups. The data might allow calculating an individual case management exposure level score, in the intervention group as well as in the control group. This will enable analyses of the outcome measures according to the per-protocol principle. Differences between patients exposed to the case management program and patients in the control condition on patient's health care utility and patient's health status will be tested using a chi-square test and student t-test, respectively. Potential confounding is checked, including the effect of different case managers and the number of patients per case manager.

## Discussion

In this paper we describe the design of a randomized controlled trial of a case management program led by a trained PN, the case manager, for comorbid T2DM patients. The project will represent a first step in the evidence about the effectiveness of a primary care based case management program by studying the effectiveness in the Dutch primary care setting of a program which has been proven feasible and acceptable in the USA. By superposing this case management program on a diabetes management program, we will also be able to identify its additional value compared to a single disease oriented management program.

We expect that better structured care based on scientific evidence and adjusted to the patients' needs and priorities can improve the quality of care coordination from both the patients' and caregivers' perspective and can result in less consumption of health care services. Patients with more than one chronic condition might need support to coordinate their care arrangements. This is reflected by the choice for quality of care as perceived by the patient as the main outcome measure. When case management superposed on diabetes management is more effective than diabetes management alone, many patients will benefit from a better organized care, better health outcomes, and more efficient use of health care services. From a societal perspective, effective case management will lead to more efficient health care utilization, and consequently lower costs.

The major strength of this study is the close fit to the normal procedure in primary care practice and the not invasive character of the case management program. Experiments with case management as proposed in this study are a logical next step in pursuing optimal care for diabetics with comorbidity, with the knowledge that more than 60% of the diabetics have one or more comorbid disorders. Also, when people get older, the prevalence of chronic illnesses increases. Taking this into account, care for comorbid diabetics can become very complex to manage. The model of case management superposed on disease management for diabetics can be seen as exemplary and it will be worthwhile to apply the results - if positive - to other single-disease management programs for other chronic diseases.

The designed program is based on the Guided Care Model which is under study in the USA. There are three major differences between the implementation of the case management program in the USA and the customized version in our study.

At first, we do not screen for eligible patients based on their health care consumption (or costs) or based on frailty measures. We have chosen to include a group of patients already enrolled in a diabetes management program, who are diagnosed with multiple chronic conditions. Because they have multiple chronic conditions, they could participate in several disease management programs. These programs aim at structuring and managing all care necessary according to the evidence-based guidelines for the specific chronic disease. However, these programs are not designed to complement each other and could increase burden and costs for the patients, especially when there are multiple comorbidities present. For that reason the question whether case management has any additional value over the structured diabetes management and if so, for which patients with comorbidity, is very important. This is also a core subject of the ZonMw research program on disease management, who provide funding for this study.

Secondly, the case manager in our study is less extensively involved in coordinating the patients' care than in the USA and for example does not coordinate transitions between sites (from hospital back to home or vice versa). When a patient is in hospital, the case manager will be informed by the patient, family or hospital. The case manager will contact the patient when he or she is still in hospital or after discharge to discuss and, if necessary, adjust the care plan. Participants in this study are not institutionalized. They are motivated and empowered during this intervention to contact the case manager if problems or changes in health status occur. Important is the emphasis on patient priorities and patient self management, monitored by monthly telephone contacts, which also implies that patients are responsible for keeping the case manager up-to-date.

Thirdly, we do not include training for the patient's informal caregivers, because the participants in this study are expected not to be severely frail. We are aware of the burden informal caregivers often face and therefore they are welcome to accompany their spouses during their participation in the case management program.

This study had some limitations in the design that might influence the reliability and validity of this study, which we have to address.

Our study population is a standardized group of T2DM patients already receiving structured diabetes care in a diabetes management program.

This could influence the external validity of the study. However at this moment the majority of the T2DM patients in the Netherlands are included in a disease management program, which means that structured diabetes management is more or less 'usual care' in primary care. Therefore we expect our study results to be generalizable, meaning it can be translated to a larger group of comorbid diabetics in the Netherlands.

We look at the additional value of the case management program next to an existing disease management program. This means that using a selected standardized population has its benefits. The patient's health is monitored every 3 months at the GP and the information in the medical records should be up-to-date.

We identify possible participants by reviewing the electronic medical record at the general practice, using disease specific (ICPC) codes. Mental illnesses such as depression are often not well recognized or diagnosed in primary care. We might miss out on patients with this condition. We expect that most participants in this study will receive the case management program tailored to somatic disorders.

In this study we trained two Practice Nurses to conduct the program. They will include 230 participants in this study, which means a caseload of 115 participants per person - half enrolled in the intervention group and half receive usual care. These participants are divided over multiple primary care practices. Differences in results between participants managed by the case managers can occur. To avoid bias due to the number of case managers we will check the data for cluster-effect by case manager.

The case managers work together with the PN and GP to discuss the results from the initial assessment and during the design of the care plan before it is presented to the patient. During this contact the GP and PN might get motivated to use specific elements in the usual care group, who do not receive the intervention. This could lead to contamination. However, the GP and PN are not involved in the program (the actual problem assessment with the patients, the monthly monitoring, the contacts between the case manager and participant) and therefore we expect this form of contamination, if it occurs, will be washed out in a short period and will not influence the intervention effect after 12 months.

This study started in October 2009 by designing the program and making all practical arrangements for the start and implementation of the intervention. In February 2011 the first patients were included in the study. Follow-up of patients will continue until July 2012.

The results of this study will become available at the beginning of 2013.

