##### Step 2) Start planning care

Together with the GP and the PN responsible for diabetes care, the case manager creates a provisional care plan. This plan is based on information from the assessment and currently provided care by the GP and PN. In case the patient's health problems results in complex care according to the GP, a multidisciplinary consultation with all relevant care providers will take place. Regular participants are the GP, PN, case manager and a representative of the DCS (a dietician or diabetes nurse).

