##### Step 3) Discussing the interim care plan with the patient

In a second consultation, the case manager will discuss the provisional care plan with the patient. The case manager will give sufficient information as a result of which the patient will be able to make decisions related to care or managing the problems found. Also, the case manager will inform the patient about community resources relevant to the patients' needs. This results in a care plan suitable to the priorities and needs of the patient and becomes definite after a final review from the GP, PN and case manager.

The care plan includes self-management activities for the patient by setting goals in an action plan (e.g. regarding nutrition, physical exercise, use of medication, and self-monitoring) tailored to the patients' capacities.

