##### Step 5) Monthly contact with the patient

The case manager will monitor the patient monthly by telephone to detect and address emerging problems regarding the implementation of the care plan and the patients' health status. If necessary, the case manager discusses these problems with the GP and takes appropriate action.

The case manager will review the patient's action plan and stimulate self-management by coaching the patient in achieving goals. The case manager will regularly update the patients' status and care plan using the notes from these contacts.

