### Sample size

The required sample size for this study is calculated on the basis of the main outcome measure, the 'tailored care' subscale of the CQ-Index. Previous research showed mean baseline scores of 3.1 (SD 1.0) on a 5-point scale [20]. We expect a mean improvement of 0.4 in the intervention group and 0.1 in the control group (mean difference in improvement 0.3). Assuming a pooled SD of change of 0.75 (SMD = 0.40), we would need complete data for 98 patients in each group; given 80% power and a significance level of 5%. We will recruit 2 × 115 patients allowing a drop-out rate of 15% during follow-up.

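### The expectation that contamination will wash out before 12 months is unsupported and partly at odds with the programme steps, and the sample size has no allowance for a diluted effect

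*Protocol article*

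**What the plan says.** Patients are randomised individually within general practices (Abstract, Methods/Design). Control patients continue to be treated by their own GP and PN (Control group).

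The Discussion names the route of contamination: the case manager talks over assessment results and care plans with the GP and PN, who might then use parts of the approach in control patients. It expects that this, if it happens, "will be washed out in a short period and will not influence the intervention effect after 12 months". The reason given is that "the GP and PN are not involved in the program", which a parenthesis narrows to the assessment with the patient, the monthly monitoring, and the contacts between case manager and participant.

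The description of the programme reads:
- Step 2: "Together with the GP and the PN responsible for diabetes care, the case manager creates a provisional care plan".
- Step 3: the care plan "becomes definite after a final review from the GP, PN and case manager".
- Step 5, where necessary: "the case manager discusses these problems with the GP and takes appropriate action".

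The Analyses section establishes effectiveness by multilevel analysis under intention to treat. It adds that the data might allow a case management exposure score in both arms, and then: "This will enable analyses of the outcome measures according to the per-protocol principle". The Sample size section rests on a "mean difference in improvement 0.3" and does not mention contamination.

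**The concern.** The Discussion dismisses contamination because the GP and PN are absent from the patient-facing tasks. But the route it names is the planning discussion, where both are present. Absence from the telephone calls does not show that this route closes. It recurs with every new intervention patient in a practice, and Step 5 can bring the GP back in at any time during the 12-month programme.

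The outcome used for the sample size, the tailored-care subscale of a questionnaire on GP care, is exposed to this route. A GP who tailors care more for control patients could raise their score on that scale. This would pull the randomised difference towards zero. If the no-influence statement stands, a null result could be read as showing no added value of case management when a reduced contrast is an alternative explanation.

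A separate matter is the possible per-protocol analysis. It is the only analysis in the article that would use exposure in the control arm, and it selects patients on something that happens after randomisation.

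**Working it through.** **1. The sections side by side**

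| Activity | GP | PN |
|---|---|---|
| Step 1, assessment with the patient | no role stated | no role stated |
| Step 2, provisional care plan | yes | yes |
| Step 3, final review of the plan | yes | yes |
| Step 5, monthly telephone call | no role stated | no role stated |
| Step 5, problems found in monitoring | if necessary | not mentioned |
| Care of control patients | yes | yes |

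The Discussion's parenthesis fits Step 1 and the calls. It does not fit the follow-up of monitoring problems with the GP, and it leaves out Steps 2 and 3.

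**2. The plan's own sample size**

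Inputs (Sample size): difference Δ = 0.4 − 0.1 = 0.3; SD of change 0.75; 80% power; 5% significance. Sidedness is not stated; two-sided reproduces the figure, while one-sided gives 78.

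n per arm = 2 × [SD × (1.960 + 0.842) / Δ]² = 2 × [0.75 × 2.802 / 0.3]² ≈ 98.1, against 98 stated.

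Drop-out: 98 / 0.85 = 115.3, against 115 recruited per arm (115 × 0.85 = 97.75). The figure is reproduced and has no reserve.

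**3. Power under dilution**

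The article gives no contamination rate, so the share c is assumed. If controls gain a share c of the effect, the ITT difference is 0.3 × (1 − c). With 98 per arm and the SD held at 0.75, the standard error is 0.75 × √(2/98) = 0.1071, and power = Φ(difference / 0.1071 − 1.96).

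| Assumed c | ITT difference | Power at 98 per arm | Complete cases per arm for 80% | Recruited per arm at 15% drop-out |
|---|---|---|---|---|
| 0% | 0.300 | 80% | 99 | 117 |
| 5% | 0.285 | 76% | 109 | 129 |
| 10% | 0.270 | 71% | 122 | 144 |
| 20% | 0.240 | 61% | 154 | 182 |
| 30% | 0.210 | 50% | 201 | 237 |

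The last two columns round up, so the first row gives 99 and 117 where the article has 98 and 115.

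**4. What selection on exposure can do**

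This is an illustration in which every setting is assumed. Compare the most exposed 70% of the intervention arm with the least exposed 80% of controls, and let exposure correlate ρ with the patient's underlying change. Mean standardised exposure is 0.348/0.7 = 0.497 in the first group and −0.280/0.8 = −0.350 in the second, a gap of 0.847. The bias is 0.75 × ρ × 0.847.

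- No true effect: ITT is 0; per-protocol is 0.064 at ρ = 0.1 and 0.191 at ρ = 0.3.
- True effect 0.3 with 20% of controls contaminated: ITT is 0.24; per-protocol is 0.36 to 0.49 over the same range.
- ρ = 0: per-protocol is unbiased, at 0.30.

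**The case against.** The Discussion is more careful than a short quotation suggests. It discloses the planning contact, qualifies what it means by not involved, and words the wash-out as an expectation should contamination occur at all. That stands: Steps 2 and 3 are acknowledged there, and the direct conflict is with Step 5, which is conditional and names only the GP. A reader might infer that the GP and PN are involved throughout, but Step 1 and the monthly calls give them no role.

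A reader might also infer that no wash-out is possible. The dates do not support that. First inclusion was in February 2011 and follow-up ends in July 2012. With a 12-month programme, entry would end around July 2011, and 12-month assessments would fall between about February and July 2012. Planning contacts probably cluster near entry, so a gap of some months is plausible. It remains an unsupported expectation, because nothing shows that a changed habit of the GP or PN fades in that time and Step 5 contact can continue.

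Third, the 10% to 30% range has no source in the article, and training, intake and coaching belong to the case manager, which limits what can spill over. That is fair: the figures show sensitivity and do not predict.

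Finally, a reader might take the per-protocol analysis as the authors' answer to contamination. The article never links the two; it is a conditional extra beside ITT. The risk of bias is the general one that attaches to any selection on exposure.

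**Conclusion.** The point holds in limited form. The statement that contamination will not influence the 12-month effect has no supporting data and is partly inconsistent with Steps 2, 3 and 5 of the programme. Contamination may dilute the ITT effect; that it does so is not established, and its size is unknown. The sample size has no room for it: power is 80% only with no dilution, and about 71%, 61% or 50% at an assumed 10%, 20% or 30%. These figures rest on a two-sided 5% test, 98 complete patients per arm, an unchanged SD of 0.75, and full benefit in the intervention arm.

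Separately, a per-protocol comparison built on the exposure score can be biased if exposure is related to prognosis, and is not biased if it is unrelated. The article gives no ground for assuming the latter.

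**What to change.** 1. Remove the statement that contamination will not influence the 12-month effect, and reconcile that paragraph of the Discussion with Steps 2, 3 and 5.
2. State that the ITT estimate may be diluted, and show power over an assumed range such as the table above.
3. Report exposure in the control arm, drawing on the activities that the Control group section already says will be monitored. The examples listed there (PN involvement, referral, medication review) are also ordinary care, so the report should say which of them count as case management exposure.
4. Keep ITT as the primary analysis.
5. If a usable exposure score is obtained in both arms, replace the per-protocol analysis with a supplementary one that uses randomised arm as the instrument: in its simplest form, the ITT difference divided by the between-arm difference in mean exposure. State its assumptions: allocation acts on the outcome only through measured exposure, exposure is measured well, and one patient's allocation does not affect another's outcome except through that measured exposure. The last is delicate when clinicians are shared. Without a usable score, label any exposure-based comparison exploratory.

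The cost is some rewording and one supplementary analysis that depends on the exposure score being obtainable. The supplementary estimate will be less precise than ITT and does not restore lost power, and the stated power will look less favourable.

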## Abbreviations

CQ-Index: Consumer Quality Index for GP care; DCS: Diabetes Care System; GC: Guided Care Model; GP: General Practitioner; HbA1c: glycated haemoglobin level; ICPC: International Classification of Primary Care; PACIC: Patient Assessment of Chronic Illness Care; PCAT: Primary Care Assessment Tool; PN: Practice Nurse; RAI-CHA: Resident Assessment Instrument - Community Health Assessment; SF-12: Short-Form 12; T2DM: type 2 Diabetes Mellitus.
